### Adverse events monitoring

Approximately 5% of caregivers of cases of CAP who have received PKD will be contacted. They will be asked about their perceptions of the medicines and cards provided in the kit, whether the child required hospitalization or improved after taking medicines and if the child had diarrhea, rash, vomiting or any other complaints. This will be done by visiting their homes.

### Ethics and research governance

This study (protocol version 2 dated 19.12.2015) has been approved by the Health Ministry Steering Committee of the Indian Council of Medical Research, New Delhi (India), the Institutional Ethics Committee, King George’s Medical University (KGMU), Lucknow (India) and relevant public authorities of state government. Written informed consent will be obtained by the project staff from all participants. To protect confidentiality of respondents, their identifiers will not be noted in any data collection instrument. Visit Log books, questionnaires, and project documents will be stored in a locked area, not accessible to unauthorized individuals.

Technical Advisory Group (TAG) for the project will be constituted to ensure quality control and government buy-in for the research findings. Members from government and non-government sectors, civil society organizations, grass root workers, academia and sponsors will be part of TAG. This group will meet twice, first at the time of project initiation and then immediately before project completion.

To ensure that the entire community of the district of Lucknow is benefitted through improved delivery of pneumonia specific health care by the public health system, PMU, PMC and PMKs will be provided to all the CHCs, APHCs, and SC of Lucknow District. This will ensure equity and distributive justice. However, there is doubt about the best way of community mobilization. The availability of better care facilities alone may drive improved care seeking for CAP. If that is the case, we have a usual care arm in our behavioral trial. If this is not the case, we will try out three other interventions, first public health facility based (CHC/APHC), second village based and the third a combination of both. The most effective strategy for improved care seeking of CAP (as a result of behavior change) will be identified and expanded into the entire district.

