## Methods/design

### Study aim

Our primary aim is to assess the effectiveness of an innovative package of orienting doctors and community health workers (CHW) about community perceptions on CAP barriers to qualified health care seeking plus infrastructural strengthening by (i) providing “Pneumonia Drug Kit” (PDK) (ii) establishing “Pneumonia Management Corner” (PMC) at additional primary health center (APHC) and (iii) “Pneumonia Management Unit” (PMU) at Community health center (CHC) *ALONG* with one of the 4 different behavior change communication (BCC) interventions:Intervention 1: Organizing Childhood Pneumonia Awareness Sessions (PAS) for caregivers of children < 5 years of age during a routine immunization day, using self-developed and validated Information, Education and Communication (IEC) materials, in PHCs and CHC monthly, conducted by a trained Auxillary Nurse Midwife (ANM) and project facilitators.Intervention 2: Organizing PAS on Village Health and Nutrition Day (V.H.N.D.) once a month by the Accredited Social Health Activist (ASHA) trained to conduct such sessionsIntervention 3: Combination of Both Intervention 1& 2Intervention 4: Usual Care

Outcome measure will be number of CAP treated by ANMs/doctors with medicines from PDK or treated at either PMC or PMU in interventions given by ANMs/ASHA workers.

Our second objective is to ascertain change, if any, in the types of health care providers’ service utilization for Acute Respiratory Illness (ARI)/CAP in last 12 months in children less than 5 years pre and post intervention.

Outcome measure will be number of ARI/CAP Treated by ANMs/doctors by various health care providers in the past 12 months in interventions given by ANMs/ASHA workers.

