### Study setting & participants

This study will be conducted in rural areas of Lucknow district, which is the capital of state of Uttar Pradesh in North India. Lucknow district has a population of 4,589,838, of which 33.79% are rural [6]. Here, there are 8 rural administrative blocks. Public health system for each of these blocks comprises of at least one (and in one block two) community health center (CHC) with outpatient care by doctors including pediatricians and 30 inpatient beds. Under each CHC are additional primary health centers (PHCs) for approximately 100,000 population with outpatient facilities and 4 beds. The lowest level of care is through a sub-center with an ANM. There is one subcenter for about 5 villages. Existing health infrastructure in Lucknow block at the initiation of the project is given in Table 1.

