### Study design

A Community Based Open Labeled Behavioral Trial conducted in 2 by 2 factorial design (Table 2) and geographic distribution of these areas is given (Fig. 1). Two blocks, proportionately equal in terms of number of ASHA workers (roughly equal to be number of villages) have been purposively paired and then randomly assigned to an interventional arm. Health infrastructure in each intervention arm is given in Fig. 2.

**Table 2 Tab2:** Design of the project

		PAS at APHCs/CHCs	
		Yes	No
PAS on VHND PLUSVillage IEC	No	Gosaiganj Block and Mall Block (Intervention1)	Bakshi Ka Talaab Block and Chinhat Block (Intervention 4)
	Yes	Malihabad Block and Mohanlalganj Block (Intervention3)	Sarojininagar Block and Kakori Block (Intervention2)

*Abbreviations PAS* Pneumonia Awareness Session, *VHND* Village Health and Nutrition Day, *IEC* information education communication, *PHC* Primary Health Centre, *APHC* Additional Primary Health Centre, *CHC* Community Health Center

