*Intervention 2:* PAS will be conducted during V.H.N.D. monthly by the ASHA worker for caregivers who congregate there using (a) case-stories (text formats) (b) messages for early recognition of pneumonia, when and where to seek care, risk perception of delayed treatment or treatment from unqualified provider and also recognition of danger signs of pneumonia through the self-developed posters, as well as (c) inform the community about infrastructural strengthening, PDK, PMC, PMU and (d) respond to queries.

*Intervention 3:* Combination of Both Intervention 1 & 2:

*Intervention 4:* This will be the Usual Care arm. In this arm only PDK, PMC and PMU will be established. No IEC will be done in the villages or APHC/CHC. Children in in the usual arm group will receive the same standard care and services provided to all children and their families residing in the area.

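### Every block receives the facility package, so the randomised comparisons estimate only the added effect of the awareness sessions, not the package effectiveness named in the primary aim

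*Protocol article*

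**What the plan says.** All places are in the protocol article.

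- **Study aim:** "Our primary aim is to assess the effectiveness of an innovative package of orienting doctors and community health workers (CHW"), together with PDK, PMC and PMU, alongside one of four communication options, of which usual care is the fourth. The outcome given with this aim counts children treated with PDK medicines or at a PMC or PMU.
- **Study setting & participants:** "Here, there are 8 rural administrative blocks".
- **Study design and Table 2:** pairs of blocks "have been purposively paired and then randomly assigned to an interventional arm". The two factors of the 2 by 2 table are PAS at health facilities and PAS on the Village Health and Nutrition Day (VHND).
- **Intervention phase, Intervention 4 (usual care):** "In this arm only PDK, PMC and PMU will be established", with no information or education activity.
- **Ethics and research governance:** "PMU, PMC and PMKs will be provided to all the CHCs, APHCs, and SC of Lucknow District". The same paragraph continues "The availability of better care facilities alone may drive improved care seeking for CAP" and then "If that is the case, we have a usual care arm in our behavioral trial".
- **Rationale for intervention:** the trial is expected to identify the smallest set of services that is effective.
- **Data management & analysis plan:** each intervention arm is compared with the control arm. Two primary outcomes are listed: the PDK/PMC/PMU count, and the choice of health provider from the baseline and end line surveys.
- **Post intervention phase:** PMC, PMU and PDK are to be handed to the state for scale-up, together with the best communication strategy.

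**The concern.** The aim names the package as the thing to be assessed, and the ethics section points to the usual-care arm when it asks whether facilities alone suffice. A comparison can inform on the package only if some blocks have it and others, at the same time, do not. Here none go without.

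The risk lies in interpretation. If the four arms come out alike, the ethics paragraph invites the conclusion that better facilities were enough. The same result would arise if nothing changed care seeking, or if use of government providers rose everywhere for unrelated reasons. The package is also what the state is to be offered for scale-up, so an unsupported statement about it would carry weight.

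**Working it through.** The protocol gives no figure to reproduce. The question is which effects the allocation can identify.

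**Inputs**

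- From Table 2, with F = facility PAS and V = VHND PAS:
  - Gosaiganj and Mall (Intervention 1): F = 1, V = 0
  - Sarojininagar and Kakori (Intervention 2): F = 0, V = 1
  - Malihabad and Mohanlalganj (Intervention 3): F = 1, V = 1
  - Bakshi Ka Talaab and Chinhat (Intervention 4): F = 0, V = 0
- From Intervention 4 and Ethics and research governance: package indicator P = 1 in all 8 blocks.

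**Step 1: comparison after the intervention**

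Model: E(Y) = μ + a·F + b·V + c·F·V + π·P, where π is the package effect. With P = 1 throughout, the arm means are:

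- Intervention 4: μ + π
- Intervention 1: μ + π + a
- Intervention 2: μ + π + b
- Intervention 3: μ + π + a + b + c

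The differences from Intervention 4 are a, b and a + b + c. π drops out of all three. In matrix terms there are 5 columns with rank 4, because the package column equals the intercept. The facility PAS effect, the VHND PAS effect and their interaction are estimable; π is not.

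**Step 2: adding the baseline survey**

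Let τ be the change that would have happened over time without the project. Before: μ in every arm. After, in Intervention 4: μ + π + τ. The change in that arm is π + τ. The design now has 6 columns and rank 5. The sum π + τ is estimable, but neither π nor τ is on its own.

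**Step 3: confirmation**

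Adding two hypothetical concurrent blocks without the package to Step 1 raises the rank to 5 of 5, and π becomes estimable. This only shows that the missing element is a package-free area. It is not a proposal to withhold the package.

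**Step 4: which outcomes have a value before the project**

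- *PDK/PMC/PMU count* (Study aim, and the first primary outcome in the analysis plan): none, since these services do not exist before the project.
- *Wider count* in the analysis plan, which adds children treated without PDK from facility stock: a value could exist. However, no abstraction of records from before the package is described; the quarterly audit is described under the intervention phase.
- *Provider choice from the surveys* (the second primary outcome): yes, baseline and end line.

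**Step 5: how clean the survey baseline is**

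The pre-intervention phase lasts 6 months and contains PMC and PMU set-up, staff training and the baseline survey. The article text does not give their order. The second objective looks back 12 months. If the survey closed the phase and set-up opened it, at most 6 of those 12 months would overlap with the package; if the survey came first, none would. Dilution of the before/after change is therefore possible and at most partial.

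The diarrhoea comparator in the analysis plan is specified for out-of-pocket spending, so it does not separate π from τ for care seeking.

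**The case against.** The strongest reply is that the protocol never plans a package-versus-no-package estimate. The aim can be read as comparing communication options on a common platform. The Discussion speaks of the effectiveness of communication strategies, the rationale speaks of finding the best one, and the planned contrast is each arm against control. The ethics paragraph justifies giving facilities to everyone on grounds of equity. Its sentence about the usual-care arm may mean only that a facilities-only arm is needed as the reference for the communication arms, which is a proper use of a control. Intervention 4 states openly what that arm receives, and scale-up is not made conditional on a package effect.

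Much of this stands. Universal provision is a legitimate choice, and the common-platform reading is what the design supports. But the aim as worded puts the package first, the rationale promises a minimum effective set of services, and the ethics paragraph ties the facilities-alone question to the usual-care arm. The text should say which question is answered.

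Three stronger readings are tempting and are not supported:

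- *That the protocol states outright that the usual-care arm will demonstrate the package effect.* It implies this; it does not say so.
- *That no before/after information exists on any primary outcome because the baseline is zero by construction.* This holds only for the PDK/PMC/PMU count. It fails for the survey outcome and for the wider treatment count.
- *That a finding of similar arms will be taken as proof that facilities suffice.* No such decision rule is written. The wording leaves room for that inference.

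**Conclusion.** The point holds as a limit on what may be concluded. The package is present in 8 of 8 blocks, so the randomised comparisons carry no information on its effect. They do identify the two PAS effects and their interaction, and that part of the design is unaffected. A facilities-alone statement can rest only on the survey change in the usual-care arm, which estimates package effect plus time trend and may be somewhat diluted by the timing of the baseline survey.

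This assumes that PDK, PMC and PMU are delivered in every block as planned. It also assumes that orientation of staff, which the aim includes in the package for all four options, is given in the usual-care arm too; the Intervention 4 description does not mention it. If it were not, the facility components would still be inseparable from the intercept.

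**What to change.** 1. In Study aim and the Abstract, restate the primary aim as the incremental effect of PAS (facility, village, both) over a facility package provided district-wide.
2. Rename the usual-care arm as facility package without PAS.
3. In Ethics and research governance, replace the sentence pointing to the usual-care arm. State instead that any facilities-alone result is an uncontrolled before/after change in that arm, taken from the planned baseline and end line surveys of government-provider use for ARI/CAP. State how the baseline survey is timed relative to package set-up.
4. In Post intervention phase, state that scale-up claims for PMC, PMU and PDK will not be based on the randomised contrast.

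This changes no allocation or data collection; the surveys are already planned. A before/after analysis from facility registers is not part of the fix, because it would need records from before the package and no such abstraction is described. The downside is a narrower claim.

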## Discussion

CAP is one of the leading killers of childhood deaths worldwide. An estimated 2 million deaths occur yearly due to community-acquired pneumonia (CAP) in children < 5 [1]. Among these about half a million die in India. Every year, approximately 43 million new cases of pediatric pneumonia are reported in India [11]. Poor and delayed care-seeking has been implicated in 6–70% of child deaths in developing countries, including those from pneumonia [12–14].

In the setting of this project we found in an earlier work that vernacular term “pneumonia” was mentioned by most caregivers regardless of age without prompting, indicating that the term had entered popular health culture. We found that recognition of pneumonia and its danger signs were poor among caregivers. In addition, it was found that fast breathing, an early sign of pneumonia, was not commonly recognized and chest in-drawing though recognized was not commonly monitored by removing a child’s clothing [3]. Limited recognition of fast breathing and chest in drawing- two key signs of pneumonia has been reported in many other studies [15–18].

As a part of an earlier work, we also found in Lucknow district that recognition of danger signs of pneumonia was poor among caregivers [19]. Caregivers reported symptoms like fever, cold, coughing as danger signs much more than Integrated Management of Neonatal and Childhood Illness (IMNCI) Danger Signs. A study conducted in Guatemala found that families are much more likely to visit a health care provider when their child experiences fever and gastrointestinal symptoms than when suffering from respiratory and other symptoms [20]. Another study in Nairobi slums reported that care-seeking from medical providers was significantly higher for diarrhea than for ARI [21]. We also found in our study that even after the disease was recognized there was a delay in seeking treatment [22].

In Lucknow district as in other districts of Uttar Pradesh and Bihar most cases CAP are taken to village-based, mostly unqualified, rural medical practitioners (RMP), and when condition deteriorates children are rushed to private clinics in towns nearby. Reasons cited for the preference of RMP included their ready availability, easy accessibility, the fact that it was culturally acceptable for women to consult these local practitioners unaccompanied by their husbands, low fees and availability of credit [3]. Systematic Review on Care-seeking practices in South Asia [23] provided evidence that families preferred remedies from traditional healers rather than skilled health workers because of cultural and religious beliefs, poor access to health facilities, and financial barriers. A study conducted in Egypt found that even though mothers were able to recognize pneumonia signs but they did not use this recognition for appropriate care-seeking [24].

In rural India RMPs are seen as appropriate doctors by caregivers, although they did not have professional training in allopathic medicine. Display and use of modern medical paraphernalia made caregivers believe that most treatment provided by RMPs results in a good outcome. Studies conducted in Northern India [3, 25, 26] and Southern India [27] also provide evidence that RMPs treat minor illnesses, provide first relief, refer patients to other providers and administer formally prescribed treatments and this makes them the first point of contact over qualified practitioners.

ASHAs, the frontline health functionaries for basic preventive care, also have an important role to play in CAP identification and referral to ANMs or higher-level public facilities. Community does seek information from the ASHAs on childhood illnesses, but ASHAs have limited knowledge about the signs of CAP and its management [3]. Even the ANMs did not have clear information on how to manage childhood pneumonia cases. Although the ANMs correctly knew how to monitor improvement/deterioration in CAP they did not feel competent enough to assess, classify and treat with minimum essential drugs before referral. The CHWs are being trained under Integrated Management of Childhood Illness (IMCI) to manage pneumonia sick child but poor supervision, inadequate essential supplies and lack of refresher trainings may affect the performance of these workers [28]. Studies conducted in other countries have, however, provided evidence that with appropriate training which emphasizes on pneumonia assessment, adequate supervision, and provision of drugs and necessary supplies, CHWs can significantly impact pneumonia specific mortality [29–32]. When we interviewed the CHWs even they were enthusiastic about learning more about CAP and participated in validation of educational messages developed by our team as a part of earlier project [3].

Community preferred health care seeking from private health facilities as compared to the government [22]. Negative perceptions of government medical facilities were related to unavailability/limited availability of necessary medicines and diagnostic tests, the perception that medicines available were of poor quality, overcrowding and referral of critical patients to distant government hospitals. A study conducted in Haryana, India explored reasons for underutilization of government health facilities. Reasons cited included lack of quality care, abominable behaviour of hospital staff, poor transportation facilities, and frequent referrals to higher centres [33]. A Nigerian study also found government facilities to be poorly managed leading to their underutilization [34]. It has been found that inadequacy in the quality of child health services in PHC facilities is a product of failures in a range of quality measures: structural i.e. lack of equipment and essential drugs and process failings i.e. non-use of the national case management algorithm and lack of a protocol of systematic supervision of health workers [35]. These structural and process factors need to be addressed so that the public health facilities are able to deliver effective services.

Many of the childhood deaths due to CAP can be averted by creating awareness in the community about signs and symptoms of pneumonia and the risk associated with it, as well as informing them about appropriate and timely care seeking. Community case management for pneumonia has associated with a 32% reduction in pneumonia specific mortality. For pneumonia, community interventions increased the care seeking behavior by 13% and the treatment failure rates also reduced by 40% [36]. Others have also shown that community interventions which are viable, effective and practical can have a sustainable impact on pneumonia specific mortality [37, 38] and neonatal mortality [39].

UNICEF, the World Health Organization (WHO) and their technical partners, developed IMCI strategy for the integrated management of five most important causes of childhood deaths including pneumonia [40]. The essential pillars of IMCI include improvement in the case management skills of health personnel, improvement in health systems, and improvement in family and community practices [41]. A study in Peru proposed informative printed media and audio-visual kits in waiting rooms of health establishments, or community education programs such as socio-drama to improve family and community practices [42]. In addition to this, Mathew JL et al. 2011 stressed the need to leverage gap in utilization of existing government health services for childhood pneumonia [43]. Therefore, we suggest that building confidence in government health staff for treating and triaging cases of CAP, possibly by timely and appropriate referral and setting up dedicated round the clock “pneumonia care units/corners” in government hospitals is urgently required.

We therefore propose this study, which assesses the effectiveness of various communication strategies for improving childhood pneumonia case management interventions at the mother/community level, health worker and health center level.

This project work will be done in partnership with the state government. This will ensure effective execution of research work. Simultaneously, capacity building of the public health staff of Lucknow district will be done. The doctors as well as ANMs/ASHA workers will be reoriented to pneumonia management plus be with community’s perception about recognition and care seeking for CAP and reasons for not opting to bring their child to public health facility as a first choice. This has not been done so far in any government program. This will ensure their emotional motivation and commitment to fight pneumonia by giving their best efforts. The project will generate demand and improve supply of quality of care of CAP and thus result in reduced mortality in Lucknow district. Since the work will be done in partnership with the government, it can be scaled up.

